## Abstract

**Background:**

The metabolic syndrome (MetS) is a risk cluster for a number of secondary diseases. The implementation of prevention programs requires early detection of individuals at risk. However, access to health care providers is limited in structurally weak regions. Brandenburg, a rural federal state in Germany, has an especially high MetS prevalence and disease burden. This study aims to validate and test the feasibility of a setup for mobile diagnostics of MetS and its secondary diseases, to evaluate the MetS prevalence and its association with moderating factors in Brandenburg and to identify new ways of early prevention, while establishing a “Mobile Brandenburg Cohort” to reveal new causes and risk factors for MetS.

**Methods:**

In a pilot study, setups for mobile diagnostics of MetS and secondary diseases will be developed and validated. A van will be equipped as an examination room using point-of-care blood analyzers and by mobilizing standard methods. In study part A, these mobile diagnostic units will be placed at different locations in Brandenburg to locally recruit 5000 participants aged 40-70 years. They will be examined for MetS and advice on nutrition and physical activity will be provided. Questionnaires will be used to evaluate sociodemographics, stress perception, and physical activity. In study part B, participants with MetS, but without known secondary diseases, will receive a detailed mobile medical examination, including MetS diagnostics, medical history, clinical examinations, and instrumental diagnostics for internal, cardiovascular, musculoskeletal, and cognitive disorders. Participants will receive advice on nutrition and an exercise program will be demonstrated on site. People unable to participate in these mobile examinations will be interviewed by telephone. If necessary, participants will be referred to general practitioners for further diagnosis.

**Discussion:**

The mobile diagnostics approach enables early detection of individuals at risk, and their targeted referral to local health care providers. Evaluation of the MetS prevalence, its relation to risk-increasing factors, and the “Mobile Brandenburg Cohort” create a unique database for further longitudinal studies on the implementation of home-based prevention programs to reduce mortality, especially in rural regions.

**Trial registration:**

German Clinical Trials Register, DRKS00022764; registered 07 October 2020—retrospectively registered.

## Background

The burden of non-communicable diseases is increasing worldwide and is among the leading causes of death [1]. The metabolic syndrome (MetS) is one of the main risk factor clusters for the incidence of metabolic and cardiovascular diseases (e.g., type 2 diabetes mellitus [2], non-alcoholic fatty liver disease [3], myocardial infarction and stroke [4]), and is also associated with the development of musculoskeletal disorders (e.g., osteoarthritis [5], tendinopathy [6]) and neuropsychiatric dysfunctions (e.g., dementia [7], depression [8]). MetS is characterized by dyslipidemia, high blood pressure, elevated blood glucose levels, and central obesity [9], and it is strongly linked to an increase in morbidity and all-cause mortality [4]. The worldwide prevalence of MetS is estimated to be around 25% [10] with an overall prevalence of up to 33% in some countries, e.g., the USA [11]. Therefore, the increasing prevalence of MetS and its secondary diseases is of considerable medical and economic relevance.

Rural regions carry a higher disease burden and have poorer health outcomes than the urban population [12]. In the USA, rural areas demonstrate a higher type 2 diabetes mellitus prevalence [13] and an elevated probability of hospital mortality compared to urban regions [14]. In comparison with other German federal states, Brandenburg, a rural and structurally weak region, demonstrates a higher type 2 diabetes mellitus prevalence with rates of up to 14.5% [15, 16]. According to the German Heart Report 2018, the mortality rate due to acute myocardial infarction in the state of Brandenburg is the highest in Germany [17]. Since the in-patient treatment of myocardial infarction in Brandenburg does not differ from that in urban regions [18], the increased mortality could be due to a high burden of risk factors and deficits in the early detection of individuals at risk. With an overall MetS-prevalence of 22% published by Moebus et al. in 2008, Brandenburg had the third highest age-standardized prevalence rate of this important risk factor complex nationwide [19]. The variations between urban and rural areas may be explained by demographic and socio-economic differences or environmental influences. Further, restricted accessibility of health care providers due to limited infrastructure, increased individual traveling times, as well as the acute shortage of physicians in rural areas may contribute to the variation [12, 13, 20–22]. It is therefore necessary to evaluate the specific causes and develop innovative strategies to overcome these challenging structural circumstances [21, 23].

Different approaches and distance-bridging procedures are currently discussed or tested. For example, by offering and coordinating individual (autonomous) traffic or structured shared transportation to the health care facilities, patient mobility is improved [24]. Furthermore, home visits realized by medical assistants and health care professionals was evaluated as a good opportunity to delegate medical care and supporting general practitioners to provide more capacity within practices and outpatient clinics [25]. Moreover, web-based consultations and telemedicine approaches, possibly in combination with home visits, could be suitable for treatment and medical care [24]. In addition, mobile physicians’ offices were rated as an appropriate alternative to local family practices and to reach patients and offer medical care in rural areas [20].

However, all these options require an individual to have been previously identified as at risk and in need of medical consultation. Therefore, only patients who have already been admitted to the health care system either because of existing diagnosis or at least conspicuous symptoms and complaints, or those who have an intrinsic motivation and awareness for medical prevention are reached. However, an earlier identification of individuals at risk is needed to effectively prevent the onset and progression of diseases.

Therefore, a decentralized time-saving and cost-effective early detection of risk factor profiles such as the MetS and its secondary diseases is deemed necessary. A mobile diagnostic procedure may be an effective approach to ensure a local, near-to-home initial screening for risk profiles at an early stage (also) in parts of the population that are insufficiently covered by existing health care structures. Patients can then be referred to appropriate health care providers and prevention, treatment, or therapy programs. Lifestyle modifications including dietary and physical activity interventions are especially efficient and cost-effective in primary and secondary prevention as well as treatment of MetS and its pathophysiological consequences [26–28]. Thus, a mobile prevention strategy, combining mobile diagnostics and the implementation of home-based lifestyle interventions, could be a promising approach.

Therefore, the aims of this study are to (1) develop and assess the reliability and validity of a setup for mobile screening and diagnostic of MetS and its secondary diseases in a pilot study, (2) test the concept and feasibility of this approach for mobile and close-to-home early diagnostic of MetS (main study part A) and its secondary diseases (main study part B) in a rural area of Germany (federal state of Brandenburg), (3) determine the prevalence of MetS (part A) and previously undiagnosed secondary diseases (part B), (4) examine any relationships of MetS with (possibly not yet established) causal, moderating and risk factors (socio-economic, lifestyle, clinical, physiological, genetic parameters) in the large (rural) sample, and (5) thereby develop a “Mobile Brandenburg Cohort” to allow future longitudinal studies. The mobile diagnostic setup and the developed “Mobile Brandenburg Cohort” will be the basis for subsequent follow-up approaches and the implementation of suitable home-based prevention strategies to reduce the incidence and prevalence of MetS and its secondary diseases.

## Methods/design

### Study design and flow

After development and validation of mobile laboratory and diagnostic units for a van and a truck (pilot study), a prospective cohort study is to be implemented: main study “part A” is a cross-sectional study, in which baseline measurements will be performed, and MetS prevalence and associated factors are to be evaluated by screening participants in a mobile diagnostic unit near to the participant’s homes. In “part B,” persons previously diagnosed with MetS in part A will be examined (mobile medical examination in a truck or phone-based interviews) to assess secondary diseases of MetS (Fig. 1). The feasibility of the mobile diagnostic approach (part A and B) is to be evaluated. All parts of the study will form the basis for the establishment of the “Mobile Brandenburg Cohort,” which will allow further longitudinal studies.

**Fig. 1 Fig1:**
[figure not shown]
Study design and flow. In the pilot study, the mobile diagnostic set-up is developed; point-of-care-analyzers are tested for validity and reliability versus a reference lab. The mobile set-up for a valid and reliable diagnosis of the metabolic syndrome (MetS) is applied in the study part A. The mobile examination unit is placed mainly at rural places across Brandenburg, and participants are recruited on-site. After inclusion, participants are examined for MetS and receive advices on physical activity and healthy nutrition for prevention of MetS and its secondary diseases. A subgroup of participants with MetS diagnosed in part A is recruited for a mobile examination regarding secondary diseases. Participants receive advices on nutrition and an exercise program at hand and they are referred to physicians for further diagnosis and treatment, if needed. Persons who are not able to participate to the mobile examination of part B are interviewed via telephone. A “Mobile Brandenburg Cohort” is established and can be continued in long-term follow-up studies

In the pilot study, setups for the mobile diagnosis of MetS (for part A) and its secondary diseases (for part B) are to be developed. On that purpose, standard methods will be transferred from clinical, stationary routines into a van or small truck that will be thus equipped like a medical examination room to set up a mobile diagnostic unit. Mobile MetS diagnosis using point-of-care analyzers will be tested for validity and reliability.

In part A, the mobile examination unit is placed at different sites in Brandenburg. Participants will be recruited locally and examined for MetS in a physician-independent, mobile setting by a health care professional. Socio-economic status, stress perception, life events, and physical activity will be assessed by approved questionnaires. The participants will receive a short, flyer-supported consultation on healthy nutrition and recommended physical activity to either prevent MetS (primary prevention) or to prevent the development of diseases (secondary prevention). The whole MetS screening and assessing of all parameters is to be limited to approximately 15 min.

In part B, participants diagnosed with MetS in part A will be recruited for a later detailed examination to check for indications of secondary diseases of MetS. Part B examinations will be also done in a mobile examination unit close to the participant’s home by a health care professional together with a physician. A detailed medical history, a clinical examination and instrumental as well as questionnaire-supported diagnostics for internal, orthopedic, cardiological, and neurological-psychiatric abnormalities will be carried out. In addition, the participants will receive a detailed consultation on healthy nutrition and a prevention exercise program directly at hand. The whole mobile clinical examination and consultation of part B will take no more than approximately 60 min. Participants who will be not eligible to mobile examination for secondary diseases will be invited to a telephone interview comprising an assessment with questionnaires that provides comparable and advanced information to the part B examinations, if procurable.

In all study parts, the participants will get their test results instantly and, if necessary due to MetS diagnosis and abnormal parameters, they will be referred to their general practitioner or a responsible medical specialist for further diagnostics and treatment.

By collecting data on MetS and its secondary diseases using mobile diagnostic units at various locations throughout the state of Brandenburg, a “Mobile Brandenburg Cohort” is to be established which can be used for further follow-up measurements with a longitudinal approach.

### Participants

To be eligible for part A, adults (men and women) with an age between 40 and 70 years will be recruited. As the study aims to implement prevention strategies to reduce morbidity and mortality of the population due to MetS, the target population for inclusion are persons with emerging risk for MetS, but less probable presence of (multiple) manifested secondary diseases. Therefore, the age range was chosen to reach participants within the working and retirement age that feature a number of age-related risks for the presence of MetS and for development of its secondary diseases [29, 30]. To be eligible for part B, participants have to be diagnosed with MetS in part A, but have to have no (known and diagnosed) secondary disease. To be eligible for all study parts, participants have to be able to understand the study information and must provide written informed consent for each part.

### Recruitment strategy

In part A, a passive recruitment strategy will be applied with a target population of all residents of Brandenburg that voluntarily approaches to the mobile diagnostic units [31]. Participants will be recruited at different locations in Brandenburg by setting up the mobile diagnostic unit in mainly rural areas far from metropolitan regions. In order to reach as many people as possible, targeted public relations work will be carried out and the mobile study unit is to be placed at market places and at events such as health days and festivals. Cooperation with companies and public administrations is planned in order to make the study known to their employees and encourage them to participate. Announcements will be done by advertising posters, articles in local newspapers and internal newsletters in companies, reports at local radio stations, and at online event calendars of communities and towns. On site, interested passers-by and participants will be directly addressed and recruited spontaneously.

For part B, potentially eligible participants who were diagnosed with MetS in part A and give consent to be re-contacted, will be recruited by telephone. Eligible persons will be allocated to the mobile examination or telephone interview in study part B.

### Sample size determination

For the pilot study (test-retest, reliability), 50 participants will be recruited. For part A and part B, sample size determination was based on the results of Moebus et al. (2008), a nationwide study on primary care patients that revealed an age-standardized MetS prevalence of 22% in Brandenburg [19]. The aim is to recruit 5000 participants in part A to develop the “Mobile Brandenburg Cohort,” and to identify approximately 1100 participants with MetS who are potentially eligible for later recruitment for part B.

### Diagnosis of metabolic risk factors

In all study parts, the MetS diagnosis is based on the definition by Alberti et al. [9] (Table 1). The mobile diagnostic approach requires spontaneous recruitment throughout the day and participants will not be always in a fasted state prior to blood sampling. Therefore, the cut-off point for elevated blood glucose is adapted according to Schipf et al. [32]. For the lipid profile, it was shown that there is little difference between fasting and non-fasting values [33] and for the estimation of an initial risk and for MetS diagnosis, also non-fasting lipids are acceptable [34]. Moreover, the more stable and meal-independent glycated hemoglobin (Hb1Ac) will be determined. It provides additional hints about impaired long-term regulation of glucose metabolism as well as helps to meaningfully assess metabolic risk factors and lipid profile even in a non-fasted state [34].

**Table 1 Tab1:** Criteria for diagnosis of the metabolic syndrome according to Alberti et al. [9]

The presence of any 3 of the following 5 risk factors constitutes a diagnosis of MetS	
Measure	Cut points/criteria
Elevated blood pressure	Systolic ≥ 130 mmHg and/or diastolic ≥ 85 mmHg [or antihypertensive drug treatment]
Elevated triglycerides	≥ 150 mg/dl [or drug treatment for elevated triglycerides]
Reduced HDL-cholesterol	Males: < 40 mg/dl, females: < 50 mg/dl [or drug treatment for reduced HDL-cholesterol]
Elevated blood glucose	≥ 100 mg/dl (fasting) or ≥ 144 mg/dl (non-fasting)* [or drug treatment for elevated glucose/type 2 diabetes mellitus]
Elevated waist circumference	Population-/country-specific, according to IDF recommendation for people with European origin: males ≥ 94 cm, females ≥ 80 cm

Abbreviations: *IDF* International Diabetes Federation, *HDL* high density lipoprotein, *MetS* metabolic syndrome

*Adaption to non-fasting blood samples according to Schipf et al. [32]

### Procedures

An overview of the methods used and parameters measured in part A and part B is presented in Table 2.

**Table 2 Tab2:** Overview of conducted measurements during the mobile examinations and the telephone interview

**Part A**	
- Metabolic syndrome diagnosis (ref. Table 1) - Glycated hemoglobin (Hb1Ac) - Pre-existing diseases and drug treatment - Body weight and body height - Socio-demographic basic information - Perceived stress (PSS-4^a^) - Life events within the last 3 months [35] - Physical activity (IPAQ-Short Form^b^)	
**Part B [mobile examination]**	**Part B [interview by phone]**
- Metabolic syndrome diagnosis (ref. Table 1)	
- Glycated hemoglobin (Hb1Ac)	
- Venous blood sample (for further analysis)	
- Body weight and body height	
- Skinfold thickness (body composition)	
- Clinical examination	
- Resting and exercise electrocardiogram	
- Pre-existing diseases and drug treatment	- Comorbidity (CCI^e^)
- Medical history	- Medical history
- Smoking (self-reported; frequency, quantity)	- Smoking (self-reported; frequency, quantity)
- Alcohol consumption (self-reported; frequency, quantity [36])	- Alcohol consumption (self-reported; frequency, quantity [36])
- Depression (PHQ-9^c^)	- Depression (modified PHQ-8^f^)
- Mild cognitive impairment (MoCA^d^)	- Amnestic mild cognitive impairment (TICS-M^g^)
	- Urbanity [37]
	- Social support (BSSS^h^)
	- Perceived stress (PSS-10^i^)
	- Childhood trauma (CTS^j^)
	- Affect (PANAS^k^)
	- Psychological well-being (PWB^l^)
	- Musculoskeletal complaints (CPG^m^, BPI^n^)
	- Risk of developing chronic pain (RSI^o^)
	- Utilization of health system [38, 39]
	- Health behavior after part A

^a^Perceived Stress Scale 4 [40]

^b^International Physical Activity Questionnaire [41]

^c^Patient Health Questionnaire 9 [42]

^d^Montreal Cognitive Assessment [43]

^e^Charlson Comorbidity Index [44]

^f^Patient Health Questionnaire 8 [45]

^g^Modified Telephone Interview for Cognitive Status [46]

^h^Berlin Social Support Scales [47]

^i^Perceived Stress Scale 10 [40]

^j^Childhood Trauma Screener [48]

^k^Positive and Negative Affect Schedule [49]

^l^Psychological Well-being Scale [50]

^m^Chronic Pain Grade Scale [51]

^n^Brief Pain Inventory [52, 53]

^o^Risk Stratification Index [35]

### Medical history

In part A, pre-existing conditions and diseases are recorded by asking about current medication to treat type 2 diabetes mellitus, hypertriglyceridemia, hypercholesterolemia, and/or hypertension, which are also inherent part of the MetS diagnosis. In addition, it is asked whether an acute or chronic coronary syndrome, stroke, coronary heart disease, renal insufficiency, or arthritis have already been diagnosed.

In part B, a comprehensive medical history (i.e., previous internal, orthopedic, cardiological, vegetative abnormalities and diseases, operations, medications, family history) as well as clinical examinations (internal medicine, orthopedic) is carried out by the physician.

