### Blood sampling and analysis

In all study parts, a blood sample (approx. 70 μl) is collected with capillary tubes after puncturing the finger bulb using safety lancets. Blood glucose as well as blood lipids (triglycerides, high-density lipoprotein cholesterol (HDL)) is analyzed simultaneously using a portable point-of-care analyzing device. During the pilot study, three different commercially available portable point-of-care analyzers (Alere Cholestech LDX, Alere GmbH, Germany; Samsung LABGEO, Samsung Healthcare, South Korea; CardioChek, PTS Diagnostics, USA) are initially compared and validated versus a certified reference laboratory including analysis of test-retest reliability and variability. The measurement device with the best reliable results for blood parameter analysis and MetS diagnosis is picked for further usage during part A and part B. Hb1Ac is also measured by using a point-of-care analyzer (Quo-Test A1C Test Kit, EKF-diagnostic GmbH, Germany).

In part B, blood samples are additionally taken from an antecubital forearm vein using a disposable needle and vacutainer. Blood is centrifuged immediately and serum samples are stored cooled for later additional analyses in a stationary laboratory, if necessary.

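### Part A counts hypercholesterolemia medication as part of the MetS diagnosis, Table 1 does not, and Table 1's clause on drugs for reduced HDL has no listed question behind it

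*Protocol article*

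**What the plan says.** The section Diagnosis of metabolic risk factors makes Table 1 the definition of MetS for all study parts. The rule is: "The presence of any 3 of the following 5 risk factors constitutes a diagnosis of MetS". Waist circumference has no drug clause. The other four components can each be met by treatment:

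- blood pressure: "or antihypertensive drug treatment"
- triglycerides: "or drug treatment for elevated triglycerides"
- HDL-cholesterol: "or drug treatment for reduced HDL-cholesterol"
- glucose: "or drug treatment for elevated glucose/type 2 diabetes mellitus"

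The section Medical history describes how part A obtains the treatment information. Participants are asked about "current medication to treat type 2 diabetes mellitus, hypertriglyceridemia, hypercholesterolemia, and/or hypertension, which are also inherent part of the MetS diagnosis".

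The section Blood sampling and analysis names the lipids measured on site: "blood lipids (triglycerides, high-density lipoprotein cholesterol (HDL)) is analyzed simultaneously using a portable point-of-care analyzing device". Total and LDL cholesterol are not in that list.

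**The concern.** Table 1 has four drug clauses and the medical history has four medication questions, but the two sets do not match. Hypercholesterolemia is asked about and described as belonging to the diagnosis, yet it is not a Table 1 criterion. Treatment for reduced HDL is a Table 1 criterion, yet no question about it is listed. Nothing in the article says what a positive hypercholesterolemia answer does to the classification.

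Four things depend on that rule:

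- the prevalence of MetS and of its components, which the Outcomes section names as part A's central result;
- entry to part B, which requires a MetS diagnosis in part A;
- the rate of newly identified MetS cases, by which the usefulness of the mobile laboratory is to be judged;
- the planned analyses of association with MetS.

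An error in classification is systematic, so a larger sample does not reduce it.

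**Working it through.** **Side-by-side comparison**

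| Medication question (Medical history) | Drug clause in Table 1 |
|---|---|
| Hypertension | Blood pressure: matches |
| Type 2 diabetes | Glucose: matches |
| Hypertriglyceridemia | Triglycerides: matches |
| Hypercholesterolemia | No such criterion |
| None listed | Reduced HDL |

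Three of the four questions match. By elimination, the hypercholesterolemia answer is the only one that could fill the HDL slot, but the article does not say that it does.

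**The plan's own figure.** Sample size determination gives 5000 participants, 22% prevalence and about 1100 cases. 5000 × 0.22 = 1100, so the figure reproduces and is not in dispute.

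**Who changes class if the answer is scored as HDL.** Five yes/no components give 2^5 = 32 patterns. Setting HDL to positive changes the diagnosis only where HDL was negative and exactly two of the other four components are present: C(4,2) = 6 of 32 patterns. All six move from no MetS to MetS. The HDL component itself changes for every treated participant who lacks a true HDL criterion, whether or not MetS changes.

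**What happens if the answer is not scored.** Participants who are treated for reduced HDL, whose measured HDL is now normal and who have exactly two other components would qualify by Table 1. With no listed question to detect them, they could be missed.

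**Algebra.** Let p be the prevalence under Table 1 applied in full, q the share wrongly added by scoring, and m the share missed by not scoring. Assume that those treated for reduced HDL would answer yes to the hypercholesterolemia question.

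- Scored: p + q
- Not scored: p − m
- Gap between the codings: q + m

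On that assumption the two codings bracket the Table 1 value.

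**When it matters against sampling error.** The 95% half-width is 1.96 × √(p(1 − p)/N), with p = 0.22 from Sample size determination.

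- N = 3,931 (enrolled, Study status): 1.96 × √(0.22 × 0.78/3931) = 0.0129, about 1.3 points
- N = 5000 (target): 1.96 × √(0.22 × 0.78/5000) = 0.0115, about 1.15 points

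At 3,931 the bias from scoring exceeds the half-width once q is above about 1.3%, or 0.0129 × 3931 ≈ 51 participants.

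**Illustration over q.** These values of q are assumptions, because the documents give no treatment rates and no distribution of components. The target N = 5000 is used so that the counts compare with the planned 1100.

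| q | Cases, 5000 × (0.22 + q) | Prevalence | Share meeting Table 1, 0.22/(0.22 + q) |
|---|---|---|---|
| 0.5% | 1125 | 22.5% | 97.8% |
| 1% | 1150 | 23% | 95.7% |
| 2% | 1200 | 24% | 91.7% |
| 3% | 1250 | 25% | 88.0% |
| 5% | 1350 | 27% | 81.5% |

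**The case against.** The strongest reply is that the article does state a scoring rule, and that rule is Table 1. The overview of measurements in Table 2 also refers the diagnosis back to Table 1 and lists pre-existing diseases and drug treatment as a separate item. On this view the sentence under Medical history describes data collection, its closing clause is a loose aside, and the coding of a questionnaire item belongs in a fuller document that is not shown.

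Part of this stands. A reader might infer that anyone on a cholesterol drug automatically meets a lipid criterion. No section says so, and no section assigns the answer to a component. A reader might also infer that the reported prevalence is necessarily too high. That holds only if the answer is scored; if it is not, the error can run the other way. A larger distortion at older ages would need treatment rates by age, which the documents do not give.

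Part B also offers some protection. The mobile examination repeats the MetS diagnosis, and a physician takes a medication history there. The telephone interview has no such repeat, and part A's prevalence is not corrected by either.

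The reply does not remove the conflict. Whether the closing clause refers to the conditions or to their medication, it places hypercholesterolemia inside a diagnosis that does not contain it. This is a disagreement between two current sections and not an omitted detail. Following Table 1 strictly does not settle it either, because the HDL drug clause then has no listed data.

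**Conclusion.** The concern holds as a contradiction in the classification rule. For participants on cholesterol medication, the article gives two incompatible accounts of what counts towards the HDL component and hence towards MetS. Scoring the answer can only add cases beyond Table 1, and not scoring it can only lose cases that Table 1 would include.

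The size and the net direction cannot be derived from the documents. What can be said is conditional: a share q moved to MetS raises prevalence by exactly q, and this exceeds the sampling half-width at 3,931 participants once q is above about 1.3%. The threshold rests on the 22% planning prevalence and on simple random sampling. Any statement that prevalence is inflated by a particular number of points would go beyond the text.

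**What to change.** Reconcile Medical history with Table 1. State for each part A medication question which Table 1 component it fulfils, or that it fulfils none, and state how the HDL drug clause is assessed when no question on treatment for reduced HDL is listed. The sponsor must choose the mapping; the documents do not settle it. Apply the one mapping to all enrolled participants. Report the prevalence of MetS and of the HDL component both with and without counting hypercholesterolemia medication.

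The cost is one coding rule and one sensitivity table, using answers already collected from the 3,931 participants. The reported prevalence may change. If treatment for reduced HDL was in fact not asked, recoding cannot recover it, and the report should say so as a limitation.
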